### Study objectives

The primary aims of this study are to evaluate whether changes in ^18^F-FDG and/or ^18^F-FLT PET in the first 7 weeks can predict progression-free survival and whether early changes (at 2 weeks) in ^18^F-FDG and/or ^18^F-FLT PET can be used for early detection of response to treatment with combined BRAF/MEK inhibitor vemurafenib plus cobimetinib compared to standard response assessment with ceCT according to RECIST v1.1 at 7 weeks.

Several secondary aims are defined in this study. The level of target inhibition is studied to whether it can predict the type (CR/PR, SD or PD) and duration of response. Molecular mechanisms of resistance will be elucidated by integrating global protein phosphorylation, genomic and cancer mutation data. The correlation between PET imaging and several key tumor characteristics at different levels is studied through a) measurements of BRAF signaling activity by immunohistochemistry (including pERK), b) analyzing DNA mutation spectrum by next-generation sequencing, c) analyzing gene expression patterns by microarray analysis and d) analyzing protein phosphorylation patterns by mass spectrometry-based phosphoproteomics. We will investigate whether differences in global phosphoprotein (including markers of BRAF pathway activity) and mutation profiles occur between sensitive and matched resistant tumor lesions and whether these profiles can predict benefit from vemurafenib/cobimetinib and resistance. Furthermore, we will investigate whether differences in protein phosphorylation patterns can be identified between pre and post treatment tumor biopsies, and whether the pre-treatment patterns would bare predictive power for response to treatment. The correlation between the pharmacokinetics of vemurafenib/cobimetinib and PET imaging is studied as well as the correlation between pharmacokinetics and therapy response. Finally, various quantitative measures of radiotracer uptake from baseline upon PET imaging are studied for predicting the type (CR/PR, SD or PD) of response, progression-free survival and overall survival.

### Study endpoints

Two primary endpoints are defined: (1) Changes in Standardized Uptake Value (SUV) of ^18^F-FDG and ^18^F-FLT PET, assessed on a continuous scale and categorized using PERCIST criteria, (2) Progression-free survival.

The secondary endpoints are as follows:Diagnostic accuracy of metabolic tracer uptake on PET in responders and non-responders.Glycolytic Index, Metabolic Tumor Volume and % Injected Dose of ^18^F-FDG/FLT on PET.Immunohistochemical analysis of tumor tissue in responders and non-responders.Changes of DNA in tumor tissue as measured by DNA deep sequencing analysis.Changes of RNA in tumor tissue as measured by RNA expression analysis.Changes of phosphoproteomic profiles in tumor tissue measured by nano-liquid chromatography coupled to tandem mass spectrometry (nanoLC-MS/MS).Changes in vemurafenib and cobimetinib drug concentrations in plasma as measured by a validated Liquid Chromotography tandem Mass Spectrometry assay.Overall Survival.ECOG Performance status.

### Overview of study design

This national multicenter prospective clinical phase II study will include approximately 90 BRAFV600E or BRAFV600 K mutation-positive patients with unresectable locally advanced or metastatic melanoma. All patients included in the study will be treated with vemurafenib 960 mg BID plus cobimetinib 60 mg QD.

The study is composed of 4 periods:
*Screening Period* during which screening procedures will take place in order to meet the inclusion criteria,
*Baseline Period* during which baseline study procedures will take place (^18^F-FDG/^18^F-FLT PET, Pharmacokinetic (PK) blood samples, tissue sampling),
*Treatment Period* during which patients are treated with vemurafenib plus cobimetinib and during which study procedures will take place,
*Follow-up Period* during which late side effects are monitored after end of treatment.

During the Screening Period, Baseline Period and Treatment Period, patients are considered ‘on study’; during Follow-up Period, patients are considered ‘off study’.

Laboratory assessments, physical examination, dermatologic examination, ophthalmology examination and cardiac evaluation will take place during the study to monitor safety and side effects of vemurafenib and cobimetinib.

All 90 patients will undergo ^18^F-FDG PET prior to treatment, 2 weeks after the initiation of therapy, at the end of the seventh week and at progression to compare to regular ceCT.

Additional PET with ^18^F-FLT will be performed at baseline, 2 weeks and at progression, PK blood samples will be collected for drug level monitoring of vemurafenib/cobimetinib and biopsies are taken for histopathological tumor characterization.

To answer all main and secondary objectives, ^18^F-FLT PET and tissue samples are only needed in a subset of patients. Therefore, this cohort is divided into three substudies:Substudy 1: 25 patients undergoing ^18^F-FDG PET, PK blood sampling, tumorbiopsies and ^18^F-FLT PET,Substudy 2: 15 patients undergoing ^18^F-FDG PET, PK blood sampling and tumorbiopsies,Substudy 3: 50 patients undergoing ^18^F-FDG PET and PK blood sampling.

Patients will be offered to participate in either one of the three substudies, depending on the wish and conditions of the patient. There is no randomization or blinding, all patients will receive the same treatment. Figure 1 shows a time schedule of the most important procedures.

**Fig. 1 Fig1:**
[figure not shown]
Study design scheme

### Study procedures

The schedule of study assessments and procedures are detailed in Table 2.

**Table 2 Tab2:** Schedule of assessments and procedures

Period	Screening	Baseline study procedures			Vemurafenib/ Cobimetinib Treatment Period									Follow-up after treatment
Cycle	Within 28 days before start therapy	Within 14 days before start therapy	Cycle1			Cycle2		Cycle3	Cycle4	Cycle5	Cycle6	Cycle7+	At progression (EoS)	Every 12 weeks
Day			1	14	15	1	21	1 (± 3)	1 (± 3)	1 (± 3)	1 (± 3)	1 (± 3)	Within 7 days (on therapy)	
In- and exclusion criteria	**X**													
Medical history and demographics	**X**													
Interval medical history		**X**			**X**	X	**X**	X	X	X	X	X	**X**	X
Physical examination	**X**	**X**			**X**	X	**X**	X	X	X	X	X	**X**	X
Vital signs (Temp, HR, RR)		X			X		X	X	X	X	X	X	X	
Pregnancy test (if indicated)	**X**													
Dermatologic examination	X					X				X		X		X
Ophthalmologic examination	if indicated													
MUGA scan	X					X				X		X	X	
12-lead electrocardiography (ECG)	X	X			X	X	X	X		X		X		
Contrast Enhanced CT (CECT)	X	**X**			**X**		**X**		X		X	X	**X**	
ECOG performance status	**X**	**X**			**X**	X	**X**	X	X	X	X	X	**X**	X
Blood samples	**X**	**X**			**X**	X	**X**	X	X	X	X	X	**X**	
Informed consent	**X**													
PK blood sample		**X**			**X**								**X**	
DNA blood sample (Substudy 1 and 2)		**X**											**X**	
^18^F-FLT PET (Substudy 1)		**X**		**X**									**X**	
^18^F-FDG PET		**X**			**X**		**X**						**X**	
Tumor biopsy (Substudy 1 and 2)		**X**			**X**								X	
Adverse events		**X**			X	X	X	X	X	X	X	X	X	X
Start vemurafenib cobimetinib			X											

**X** *= Assessment/procedure performed to meet the objectives of the study,* X = *Assessment/procedure performed to monitor vemurafenib/cobimetinib treatment*

#### Screening and baseline period

After signing informed consent, patients will undergo screening procedures that include testing for the BRAFV600 mutation; laboratory tests (hematology, chemistries, LFTs); 12-lead ECG; left- ventricular function evaluation (MUGA), contrast-enhanced magnetic resonance imaging (MRI) or CT scan of the brain; contrast-enhanced CT of the chest, abdomen, and pelvis; and dermatologic assessments. After registration patients will undergo baseline procedures prior to the Treatment Period, including ^18^F-FDG PET, ^18^F-FLT PET (Substudy 1), PK blood sampling and tissue sampling (Substudy 1 and 2).

#### Study medication

During the Treatment Period vemurafenib will be taken orally at a starting dose of 960 mg BID, starting on Day 1 to Day 28 of each 28-day treatment cycle. Cobimetinib will be taken orally 60 mg once daily starting on Day 1 to Day 21 of each 28-day treatment cycle.

All patients will be closely monitored for safety and tolerability during all cycles of therapy, at the end-of-study treatment visit, and during the follow-up period. Treatment will continue until disease progression, death, unacceptable toxicity, or withdrawal of consent, whichever occurs earliest.

In patients with confirmed progressive disease according to RECIST v1.1 study treatment is discontinued when no benefit for the patient is expected anymore.

#### Response assessment

Tumor response will be evaluated with ceCT scans of neck, thorax, abdomen and pelvis according to RECIST v1.1. Any evaluable and measurable disease must be documented at screening and re-assessed at each subsequent tumor evaluation. The ceCT scans are performed at baseline, 2 weeks after start study medication, at the end of the seventh week, every 8 weeks thereafter and at progression following standard protocol. CT/MRI scans may be repeated at any time if progressive disease is suspected.

#### ^18^F-FDG and ^18^F-FLT PET imaging

In all 90 patients ^18^F-FDG PET scans are performed at baseline, Day 15 of Cycle 1, Day 21 of Cycle 2 and at progression. In 25 patients additional ^18^F-FLT PET scans are performed at baseline, Day 14 of Cycle 1 and at progression. Participating PET imaging sites must have the EARL FDG-PET/CT accreditation prior to the start of the study, and perform the PET scans to meet the standard requirements indicated in the European Association of Nuclear Medicine (EANM) guideline ‘FDG PET and PET/CT: EANM procedure guideline for tumour PET imaging: version 1.0’ [53]. All PET/CT scans are DICOM sent for central reviewing. All images will be assessed visually to identify sites of increased uptake. For quantification, a software package is used, which is developed for the specific purpose of quantifying PET images [54]. In all images, standardized uptake values (SUV) will be calculated for both ^18^F-FDG and ^18^F-FLT PET studies of sites showing the highest uptake. To evaluate and correlate both PET studies, but also to correlate the results of follow-up studies, a low-dose CT scan for attenuation correction will be used to make a head to head comparison between the uptake at different sites feasible.

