### Patient population

BRAFV600E or BRAFV600K mutation-positive patients with unresectable locally advanced or metastatic melanoma will be included in the trial. Inclusion and exclusion criteria are listed in detail in Table 1, written informed consent is required for inclusion.

**Table 1 Tab1:** Inclusion and exclusion criteria

Inclusion criteria	Exclusion criteria
***Disease-Specific Inclusion Criteria:*** • Histologically confirmed melanoma, either unresectable stage IIIc or stage IV metastatic melanoma, as defined by AJCC 7th edition. • Naïve to treatment for locally advanced unresectable or metastatic disease (i.e., no prior systemic anti-cancer therapy for advanced disease; stage IIIc and IV). Prior immunotherapy (including ipilimumab) is allowed. • Documentation of BRAF^V600E^ or BRAF^V600K^ mutation-positive status in melanoma tumor tissue. • Measurable disease per RECIST v1.1, which are accessible to biopsies. • Biopsy lesion is within scan reach of contrast enhanced CT and PET/CT. • ECOG performance status of 0 or 1. • Consent to undergo tumor biopsies of accessible lesions.	***Cancer-Related Exclusion Criteria:*** • History of prior RAF or MEK pathway inhibitor treatment. • Palliative radiotherapy, major surgery or traumatic injury within 14 days prior to the first dose of study treatment. • Active malignancy other than melanoma that could potentially interfere with the interpretation of efficacy measures.
	***Exclusion Criteria Based on Organ Function:*** • History of or evidence of retinal pathology on ophthalmologic examination that is considered a risk factor for neurosensory retinal detachment, retinal vascular occlusion, or neovascular macular degeneration. • History of clinically significant cardiac dysfunction, including current unstable angina, symptomatic congestive heart failure (NYHA classII), history of congenital long QT syndrome or mean QTcF >450 msec at baseline or uncorrectable abnormalities in serum electrolytes, uncontrolled hypertension ≥ Grade 2, left ventricular ejection fraction (LVEF) below institutional lower limit of normal (LLN) or below 50%. • Patients with active CNS lesions, except when all known CNS lesions have been treated with stereotactic therapy or surgery, AND there has been no evidence of clinical and radiographic disease progression in the CNS for ≥3 weeks after radiotherapy or surgery.

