#### Tissue sampling for tumor characteristics

To evaluate the extent of inhibition of mutant BRAF, we will monitor the activity of the pathway in tumor tissue samples of 40 patients. Easily accessible progressive target lesions according to RECIST v1.1 will be biopsied before treatment, during treatment (*t* = 2 weeks) and at the time of proven progression. Tumor biopsies will be partly frozen or formalin fixated. Frozen tissue will be used for RNA extraction for RNA sequencing, genomic DNA extraction, next-generation sequencing and for phosphoproteomics, formalin fixed paraffin embedded material will be used for immunohistochemic analysis.

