Biopsies will be performed in a subset of 40 patients. This number is based on the paper of Dobbin and Simon 2007 in which sample sizes are calculated for building predictors [57]. The simulations indicated that with 2 differentially expressed genes, and 40 patients an effect size (2δ/σ) of 1.5 or more and with one differentially expressed gene, an effect size of 1.7 or better could be obtained.

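### SUV sites are chosen by highest uptake and biopsy sites by accessibility, with no rule to measure SUV in the biopsied lesion, so the secondary PET-tissue correlation may pair different lesions

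*Protocol article*

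**What the plan says.** **Where uptake is measured.** The section on FDG and FLT PET imaging begins with a visual reading: "All images will be assessed visually to identify sites of increased uptake". For quantification it says that "standardized uptake values (SUV) will be calculated for both ^18^F-FDG and ^18^F-FLT PET studies of sites showing the highest uptake". It adds that a low-dose CT is used "to make a head to head comparison between the uptake at different sites feasible". Scans are sent for central review.

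**Where tissue is taken.** The section on tissue sampling says: "Easily accessible progressive target lesions according to RECIST v1.1 will be biopsied before treatment". The biopsy is repeated at two weeks and at proven progression. On numbers, the sample size section says: "Biopsies will be performed in a subset of 40 patients". These are Substudy 1 (25 patients, who also have FLT PET) and Substudy 2 (15 patients). Table 1 adds an eligibility criterion: "Biopsy lesion is within scan reach of contrast enhanced CT and PET/CT".

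**What is to be related.** Among the secondary aims in Study objectives: "The correlation between PET imaging and several key tumor characteristics at different levels is studied". The characteristics are BRAF signalling by immunohistochemistry, the mutation spectrum, gene expression and protein phosphorylation. Study endpoints also lists "Glycolytic Index, Metabolic Tumor Volume and % Injected Dose of ^18^F-FDG/FLT on PET", without naming the region on which these are measured. Neither the objectives nor the statistical analysis section says whether the lesion or the patient is the unit of the PET-tissue correlation.

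**The concern.** The two selection rules use different criteria. Intensity of uptake decides where SUV is measured; access and RECIST target status decide where tissue is taken. Uptake plays no part in the choice of biopsy lesion, and being biopsied plays no part in the choice of SUV site.

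In a patient with one lesion the two rules must agree. In a patient with several they may not. A superficial lesion could be biopsied while the hottest measured sites lie elsewhere. That patient would contribute uptake from one tumour and molecular data from another.

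At stake is the interpretation of the PET-tissue aim. If lesions within a patient differ in uptake, such pairing is expected to pull the observed correlation towards zero. A weak result would then be hard to read: it could mean that PET does not reflect the biology, or that the two were measured in different places. The subset is small and its tissue comes from serial invasive biopsies, so avoidable dilution is worth preventing.

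**Working it through.** **1. The plan's own figure.** The plan gives no figure for the PET-tissue correlation. Its main calculation reproduces: for a hazard ratio of 0.5, two-sided 5%, 80% power and a 50-50 split, events = 4 × (1.960 + 0.842)² / (ln 2)² ≈ 65.3, rounded up to the stated 66. That calculation concerns PFS by patient-level PET group and does not depend on which lesion is biopsied. The 40 biopsy patients were sized for building predictors, not for a correlation test.

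**2. The rules side by side.**

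| Step | Selection rule in the text | Ensures that SUV and tissue come from the same lesion? |
|---|---|---|
| Visual PET reading | All sites of increased uptake | No; yields no SUV |
| SUV | Sites of highest uptake, number not given | Only if the biopsied lesion is among them |
| Low-dose CT | Makes comparison between sites feasible | No; does not add the biopsied lesion to the measured set |
| Biopsy | Accessible, progressive RECIST target lesions | No; uptake is not a criterion |
| Table 1 | Biopsy lesion within CT and PET/CT reach | No; makes measurement possible, does not require it |

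No row requires SUV in the biopsied lesion, and no row rules it out.

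**3. Timing.** Table 2 places biopsies at baseline, Day 15 of Cycle 1 and progression. FDG PET is done at the same three points, and FLT PET at baseline, Day 14 and progression. Scans therefore already exist for each biopsy time point.

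**4. Scale, for illustration.** None of the correlations below is in the document. Let ρ be the correlation between uptake and a tissue marker within one lesion, and κ the correlation of uptake between the measured and the biopsied lesion. Assume the marker relates to uptake elsewhere only through uptake in its own lesion. If every patient is mismatched, observed r = ρ × κ. Power at two-sided 5% is Φ(atanh(r) × √(n − 3) − 1.96).

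With ρ = 0.6 and n = 40, √37 = 6.083:
- No mismatch: r = 0.60, atanh = 0.693, power = Φ(2.26) ≈ 0.99.
- κ = 0.7: r = 0.42, atanh = 0.448, power = Φ(0.76) ≈ 0.78.
- κ = 0.5: r = 0.30, atanh = 0.310, power = Φ(−0.08) ≈ 0.47.

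If only half the patients are mismatched, r is roughly 0.6 × (0.5 + 0.5κ):
- κ = 0.7: r = 0.51, power ≈ 0.93.
- κ = 0.5: r = 0.45, power ≈ 0.84.

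With ρ = 0.5 and every patient mismatched:

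| κ | Observed r | Power, n = 40 | Power, n = 25 (FLT) |
|---|---|---|---|
| 1.0 | 0.50 | 0.92 | 0.73 |
| 0.8 | 0.40 | 0.73 | 0.51 |
| 0.6 | 0.30 | 0.47 | 0.31 |
| 0.4 | 0.20 | 0.23 | 0.16 |

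There is no loss in patients whose biopsied lesion is among the measured sites, provided that lesion's own value is the one used.

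**The case against.** The strongest reply is that the text excludes nothing. The measured sites are plural and unnumbered, so the biopsied lesion may be one of them. It is a RECIST target lesion, not merely a convenient one, and Table 1 requires it to be in scan range, plausibly so that tissue and imaging can be linked. An article also condenses a fuller protocol, where region-of-interest rules usually sit. Finally, the Background describes many resistance mechanisms but does not say that lesions within one patient differ, and the study calls itself explorative.

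Much of this stands, and it limits the point. A reader might infer that SUV is taken solely at the hottest sites, or that the PET-tissue analysis does correlate different tumours. The text supports neither: it contains no such restriction, and mismatch is a possibility whose frequency is unknown. A reader might also infer that FDG and FLT will be compared at different sites. The low-dose CT provision is there to relate the two PET studies site by site and largely meets that worry. The remark about FLT background in liver and bone marrow does not show that the hottest tumour site differs between tracers.

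What does not stand is that this is mere omission. The article states a measurement rule based on intensity, and that rule does not by itself serve a stated aim. Being in the field of view, or being seen on visual reading, does not give the lesion an SUV.

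**Conclusion.** The point holds as a limited one. SUV sites and biopsy sites are selected by different criteria, and the text has no rule that joins them. The secondary PET-tissue correlation may therefore pair different lesions in patients who have several, and may be weakened as a result.

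The document does not allow the loss to be sized. The illustrative power values depend on assumed within-lesion and between-lesion correlations and on the share of patients mismatched; the lower ones assume mismatch in everyone. They show that the loss could range from negligible to substantial, and should not be read as an estimate.

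The primary aims on PFS and early response, the 66 events and the 90 patients are untouched. This is an inexpensive improvement to a secondary, exploratory aim, not a flaw in the trial's main design.

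**What to change.** For Substudies 1 and 2, add a rule that central review also measures SUV (mean, peak and max) in the biopsied lesion on the existing FDG and FLT scans at the biopsy time points: baseline, about two weeks, and progression. Use that lesion-level value for all PET-tissue correlations. Keep the highest-uptake value for the PFS analyses.

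The cost is one extra region of interest per existing scan in 40 patients: at most 40 × 3 = 120 FDG regions and 25 × 3 = 75 FLT regions, 195 in all. The number is lower where a patient has no progression scan or the lesion is already among the measured sites. The location of each biopsied lesion must be passed to the central reader. No extra scan, biopsy or reader is needed, and the measurement can be made retrospectively on stored images.

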#### Blood samples for pharmocokinetics

At baseline, Day 15 of Cycle 1 and at progression blood will be collected just before intake of the morning dose of vemurafenib and cobimetinib for pharmacokinetic purpose.

In a subset of patients treated in the Netherlands Cancer Institute (approximately *n* = 25), blood samples for a whole PK curve (pre-dose, 1 h, 2 h, 3 h, 4 h, 6 h and 8 h post-dose) will be collected on Day 15 of Cycle 1.

#### Blood samples for DNA sequencing

A peripheral blood sample is obligated for all patients who will undergo histological biopsy for DNA sequencing. Therefore, 1x10mL blood will be drawn at baseline and at the time of progression.

#### Tissue sampling for tumor characteristics

To evaluate the extent of inhibition of mutant BRAF, we will monitor the activity of the pathway in tumor tissue samples of 40 patients. Easily accessible progressive target lesions according to RECIST v1.1 will be biopsied before treatment, during treatment (*t* = 2 weeks) and at the time of proven progression. Tumor biopsies will be partly frozen or formalin fixated. Frozen tissue will be used for RNA extraction for RNA sequencing, genomic DNA extraction, next-generation sequencing and for phosphoproteomics, formalin fixed paraffin embedded material will be used for immunohistochemic analysis.

